## Abstract

**Background:**

Ixekizumab, an interleukin 17A inhibitor, has demonstrated efficacy in improving clinical and patient-reported outcomes in axial spondyloarthritis (axSpA) and psoriatic arthritis (PsA). However, objective data regarding its effects on peripheral inflammation in joints and entheses, inflammation of the posterolateral spinal segments, and structural progression in the spine are lacking. In this study, we aim to address the abovementioned gaps by conducting a longitudinal investigation of the effects of ixekizumab on peripheral and axial inflammation and structural damage in patients with axSpA and PsA. Through comprehensive assessment using advanced imaging techniques such as whole-body magnetic resonance (WB-MRI) and detailed MRI evaluation of the spine, including MRI-based synthetic computed tomography (synthetic CT), and low-dose CT, we seek to investigate the therapeutic effectiveness of ixekizumab across different disease domains.

**Methods:**

DAPHNE (EU-CT 2024-510746-14–00) is a 2-year open-label investigator-initiated multi-center study conducted in Denmark. Sixty-five patients with axSpA and PsA (≥25 with each diagnosis; ≥10 PsA patients with imaging-documented axial involvement), with a clinical indication for biological disease-modifying antirheumatic drug therapy, will be treated with ixekizumab, and followed by clinical, laboratory, WB-MRI, radiography, and low dose CT of sacroiliac joints (SIJs) and spine. MRI will include T1-weighted and short tau inversion recovery (STIR) sequences and a sequence allowing the generation of CT-like “synthetic CT” MR images. Images will be evaluated by readers blinded for diagnosis and clinical and other imaging findings. Furthermore, new lesion definitions and evaluation methods for synthetic CT and low-dose CT will be sought developed and explored.

**Discussion:**

Currently, there are no data on the objective assessment of enthesitis, inflammation of the posterolateral segments of the spine, or structural progression in the spine using modern imaging during ixekizumab treatment neither in PsA nor axSpA. Thus, a longitudinal study hereof - the DAPHNE study - is anticipated to significantly improve our understanding of the diverse disease manifestations in axSpA and PsA, and how they respond to ixekizumab treatment. Additionally, the study will provide valuable insights into new and improved imaging examination and evaluation methods.

**Clinical trial number:**

EU-CT 2024-510746-14-00.

## Introduction

Spondyloarthritis (SpA) comprises a group of inflammatory rheumatic diseases, including axial spondyloarthritis (axSpA) and psoriatic arthritis (PsA), characterized by inflammation affecting axial and peripheral joints as well as entheses [1]. The diverse manifestations of SpA cause pain, fatigue, and functional impairment [2–4]. Nevertheless, conventional clinical and radiographic assessments often lack sensitivity and specificity, particularly in diagnosing enthesitis, a hallmark pathology in PsA and axSpA [5].

Ixekizumab, an interleukin 17A inhibitor, has demonstrated efficacy in improving clinical and patient-reported outcomes in axSpA and PsA [6–9]. However, objective data regarding its effects on peripheral inflammation in joints and, most importantly, entheses is lacking.

Imaging modalities such as ultrasonography and magnetic resonance imaging (MRI) can visualize inflammation in peripheral entheses and joints [10]. Whole-body MRI (WB-MRI) presents a comprehensive approach to assess both peripheral and axial manifestations in a single examination [11, 12]. Validated assessment methods for WB-MRI in SpA patients, as the OMERACT MRI Whole-Body Score for Inflammation in Peripheral Joints and Entheses (MRI-WIPE) [13, 14], provide valuable tools for objective evaluation in addition to differentiating PsA and axSpA manifestations and their response to therapy.

Patients with axSpA and axial PsA demonstrate inflammation and damage at various anatomical locations in the spine on MRI, including the vertebral bodies and the “posterior segments” of the spine, i.e. the costo-transversal joints, costo-vertebral joints, facet joints, spinous/transverse processes, and the surrounding soft tissue [15, 16]. While methods like the Spondyloarthritis Research Consortium of Canada (SPARCC) MRI Spine index and the Berlin modifications of the ASspiMRI-a have been validated and are often used in clinical trials [17, 18], they do not capture inflammation in posterior segments of the spine or in general provide detailed anatomical information as they do not record where in the vertebral bodies the inflammation is located. The Canada-Denmark (CANDEN) MRI assessment method for spinal lesions offers a more comprehensive approach, enabling detailed evaluation of various anatomical locations within the spine, including the posterior segments of the spine [19, 20]. Currently, there are no data regarding the effectiveness of ixekizumab on spinal inflammation as assessed by this detailed method.

Assessing structural progression in the spine in patients with SpA, which is crucial for determining a therapy’s structure-modifying effects, remains a challenge. Conventional radiography using the modified Stoke Ankylosing Spondylitis Spinal Score (mSASSS) [21] lacks sensitivity to change [22] and cannot adequately assess structural damage progression in short-term trials (≤2 years) [23, 24]. Computed tomography (CT) offers superior visualization of structural damage [25] but is limited by radiation exposure. A promising alternative is MRI-based synthetic CT (sCT) [26], which provides CT-like images without radiation exposure. However, its utility in assessing structural damage progression in the spine in patients with axSpA and PsA remains unexplored.

In this study, we aim to address the abovementioned gaps by conducting a longitudinal investigation of the effects of ixekizumab on peripheral and axial inflammation and structural damage in patients with axSpA and PsA. Through comprehensive assessment using advanced imaging techniques such as WB-MRI and detailed MRI evaluation of the spine, including sCT, and low-dose CT, we seek to provide valuable information on the therapeutic effectiveness of ixekizumab across different disease domains. The primary objective is to assess the effect of ixekizumab on the total inflammatory burden in the entire body (peripheral and axial joints and entheses) of patients with axSpA and PsA, as assessed by WB-MRI.

Here we report the design of the DAPHNE study.

## Methods/Design

### Study design

DAPHNE (EU-CT 2024 -510746-14–00) is a 2-year open-label investigator-initiated multi-center study conducted in Denmark. Sixty-five patients with axSpA and PsA (≥25 with each diagnosis; ≥ 10 PsA patients with imaging-documented axial involvement), with a clinical indication for biological disease-modifying antirheumatic drug (DMARD) therapy, will be treated with ixekizumab, and followed by clinical and laboratory examination (months 0, 2, 4, 6, 9, 12, 18, 24), WB-MRI (months 0, 4, 12 and 24), radiography (months 0 and 24) and low dose CT of sacroiliac joints (SIJs) and spine (months 0, 12 and 24) (see Fig. 1). MRI will include T1-weighted and short tau inversion recovery (STIR) MRI and a sequence allowing the generation of CT-like “synthetic CT” MR images.

**Fig. 1 Fig1:**
[figure not shown]
Design of the DAPHNE study. *PsA *psoriatic arthritis, *AxSpa* axial spondyloarthritis, *CT* computed tomography, *SIJs* sacroiliac joints, *WB-MRI* whole Body magnetic resonance imaging, *STIR* short tau inversion recovery, *synthetic CT* MRI-based synthetic computed tomography, *BASDAI* the bath ankylosing spondylitis disease activity index, *BASFI* the bath ankylosing spondylitis functional index, *ASAS* assessment in SpondyloArthritis International society, *DAS* disease activity index, *DAPSA* disease activity index for psoriatic arthritis, *BASMI* the bath ankylosing spondylitis metrology index, *ASDAS* ankylosing spondylitis disease activity score, *CRP* C-reactive protein, *BSA* Body surface area, *HLA-B27*, human leukocyte antigen B27, *anti-CCP* anti-citrullinated protein, *RF* rheumatoid factor. Dark arrows: Major assessment visits

### Study interventions

All patients (axSpA and PsA) will be treated with ixekizumab. The study medicine will be provided as prefilled pens with ixekizumab 80 mg dispensed in 1 ml sterile water. At week 0 (baseline) the patients are treated with subcutaneous (sc.) ixekizumab 160 mg (2 injections of 80 mg), thereafter 80 mg at week 2 and week 4. From week 4 and throughout the study the patients are treated with sc. ixekizumab 80 mg every 4 weeks. The first sc. injections of ixekizumab will be given at the participating centers under the supervision of a study nurse. Hereafter, the patient will be allowed to self-administer the study medicine at home.

Patients are allowed to continue the following concomitant medications: conventional synthetic (cs) DMARDs (dose must be fixed from 1 month before the first MRI scan to month 4), non-steroid antirheumatic drugs (NSAID) (dose must be fixed from 1 month before the first MRI scan to month 4), and paracetamol. Injections of glucocorticoids in peripheral joints and/or entheses should preferably be avoided and are only allowed at specific time points during the study; these periods are before 1 month before the first MRI scan, from month 4 (after all study procedures have been performed) to month 11, and from month 12 (after all study procedures have been performed) to month 23.

Other drugs with a potential disease-modifying effect (except csDMARDS) and high-potency opioid analgesics for musculoskeletal pain are prohibited during the study.

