### Assessments

During the 2-year study period, patients will have eight visits to the outpatient clinic, three of which are major assessment visits (months 4, 12, and 24) (see Fig. 1, dark blue arrows). At the major assessment visits, treatment efficacy, and disease activity are evaluated. Patients with ASDAS low disease activity (ASDAS ≤2.1) (axSpA) or DAPSA low disease activity (DAPSA ≤14) (PsA) continue treatment with sc. inj. ixekizumab 80 mg every 4 weeks. Patients, who are not responding (defined as having ASDAS > 2.1 or DAPSA > 14), change treatment at the discretion of the treating rheumatologist and according to the available guidelines from the Medicine Council, Danish Regions (Medicinrådet, Danske Regioner), and they continue to be followed in the study.

All protocol-related assessments will be entered into an electronic case report dedicated to the DAPHNE study.

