#### Other assessments

Details of other assessments (clinical, composite, and patient-reported assessments) are provided in Table 1 and a summary of all measures to be collected is provided in Table 2.

**Table 1 Tab1:** Details of clinical, composite and patient-reported assessments

Clinical evaluation and composite indices	
Inflammatory back pain (ASAS definition)	Criteria set for inflammatory back pain according to ASAS experts include age at onset < 40 years, insidious onset, improvement with exercise, no improvement with rest, and pain at night [35].
ASDAS CRP	A composite measure of disease activity based on CRP, VAS of patient global assessment of disease activity (0–100 mm), back pain (0–100 mm), duration of morning stiffness (0–100 mm), and peripheral pain/swelling (0–100 mm) [36].
BASMI	Five measurements of different movements are performed, including intermalleolar distance, flexion and lateral flexion of the lumbar spine, tragus-wall distance, and rotation of the neck [37].
DAS28 CRP	An index based on tender and swollen joint count of 28 peripheral joints, patient global assessment of disease activity, and CRP [38].
CDAI	CDAI is a composite index based on tender and swollen joint count and patient and physician global assessment of disease activity on VAS [39].
Swollen and tender joint count	In total 66 joints are examined for swelling and 68 for tenderness in all patients. The following joints are examined: right and left temporomandibular joint, sternoclavicular joint, acromioclavicular joint, glenohumeral articulation, elbow joint, wrist, 10 MCP joints, 10 PIP- and DIP joints in the hands and 10 toes and MTP-joints, tarsus/midfoot joint, ankle joint, knee joint, hip joint (for tenderness only).
SPARCC Enthesitis Index	SPARCC Enthesitis index comprises 18 anatomical sites, nine on the right side and nine on the left side: Insertion of supraspinatus, lateral and medial epicondyle humerus, greater trochanter, quadriceps insertion into the superior border of patella, patellar tendon insertion into the inferior pole of patella or tibial tubercle, Achilles tendon and insertion plantar fascia, with a score of 0–16 (for scoring purpose, the inferior patella and tibial tuberosity are considered one site because of their anatomical proximity) [40].

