### Endpoints

#### Primary endpoint

The primary endpoint is the change from baseline to month 12 in the total inflammatory burden in the entire body (peripheral and axial joints and entheses), as assessed by WB-MRI, in patients with axSpA and PsA treated with ixekizumab.

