**Other secondary endpoints**	
1.	Change from baseline to *months 4, 12, and 24* in *axial inflammation*, as assessed by MRI, in patients with axSpA and PsA treated with ixekizumab, including separately in the posterolateral elements of the spine (facet joints, costovertebral joints, transverse processes, spinous processes, and perientheseal soft tissues) and in the vertebral bodies.
2.	Change from baseline to *months 4 and 24* in *peripheral enthesitis*, as assessed by WB-MRI, in patients with axSpA and PsA treated with ixekizumab.
3.	Change from baseline to *months 4 and 24* in *peripheral joint inflammation*, as assessed by WB-MRI, in patients with axSpA and PsA treated with ixekizumab.
4.	Change from baseline to *month 4* in *total inflammatory burden in the entire body* (peripheral and axial joints and entheses), as assessed by WB-MRI, in patients with axSpA and PsA treated with ixekizumab.
5.	*Description of differences between axSpA and PsA* inflammatory disease manifestations and their response to ixekizumab therapy at months 4, 12, and 24 (by sacroiliac joint and spine MRI and by WB-MRI).
6.	*Development of improved MRI and CT assessment methods* for axial structural damage assessment.
7.	Description of the *relationship between clinical, patient-reported, and imaging findings* at baseline and during ixekizumab therapy.

*WB-MRI* Whole body magnetic resonance imaging, *axSpA* axial spondyloarthritis, *PsA* Psoriatic arthritis, *CT* computed tomography

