### Statistical analysis

The primary analysis will be the intention-to-treat (ITT) population, which comprises all included patients. An additional Per Protocol (PP) analysis will be done as a robustness analysis. The entire patient population will be analyzed for the primary and secondary endpoints. Furthermore, patients will be stratified based on their diagnosis and WB-MRI remission status (remission versus non-remission). Additionally, patients will be stratified as clinical responders versus non-responders at months 4, 12, and 24, based on the presence/absence of ASDAS low disease activity (≤2.1) for patients with axSpA and DAPSA low disease activity (≤14) for patients with PsA. The total inflammatory burden in the entire body, including both peripheral and axial joints and entheses will be assessed at multiple time points - month 0 (baseline), month 4, month 12 (the primary endpoint), and month 24. The total inflammatory burden in the entire body and the WB-MRI remission status will be determined using the sum score of WB-MRI scoring methods for peripheral (WIPE) and axial (CANDEN spine and SPARCC SIJ) inflammation. Further, patients (both the entire patient population and sub-groups stratified by diagnosis, WB-MRI remission and clinical responsiveness) will be evaluated separately for peripheral enthesitis and joint inflammation (using WIPE), and axial inflammation (using CANDEN spine and SPARCC SIJ).

The statistical analyses will include descriptive statistics for all patients (number, median/mean/range of conventional and experimental data), comparisons between groups and within groups (axSpA vs. PsA, WB-MRI remission vs. WB-MRI non-remission, and clinical responders vs. clinical non-responders).

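### The fixed-dose rule for csDMARDs and NSAIDs ends at month 4, so background treatment can change before the month-12 primary scan in patients who continue ixekizumab

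*Protocol article*

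**What the plan says.** All statements are from the protocol article.

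- **Background drugs (Study interventions).** Patients may continue "conventional synthetic (cs) DMARDs (dose must be fixed from 1 month before the first MRI scan to month 4"), and NSAIDs under the same limit. csDMARDs are exempt from the ban on other disease-modifying drugs. The exclusion criteria (Participants) ask only that DMARD doses be stable for a month before the first MRI.
- **Local glucocorticoid injections (same paragraph).** One permitted period runs "from month 4 (after all study procedures have been performed) to month 11", which leaves a clear month before the month-12 scan.
- **Primary endpoint.** "The primary endpoint is the change from baseline to month 12 in the total inflammatory burden in the entire body". All patients receive ixekizumab, and the comparison is within patients.
- **Month 4 decision (Assessments).** Patients in low disease activity continue ixekizumab. Those who are not "change treatment at the discretion of the treating rheumatologist" and remain in follow-up.
- **Analysis (Statistical analysis).** "The primary analysis will be the intention-to-treat (ITT) population, which comprises all included patients". Robustness is to be checked in a per-protocol set.
- **Month-4 scan (Table 3, other secondary endpoint 4).** "Change from baseline to *month 4* in *total inflammatory burden in the entire body" is already planned.

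**The concern.** The stated objective is the effect of ixekizumab on total inflammatory burden. With one arm, any other treatment change between baseline and month 12 becomes part of the measured change. The dose rule protects the first 4 months of that interval and leaves the last 8 open.

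Month 4 is a natural point to release patients who change treatment, but the rule also ends for those who continue ixekizumab to the primary scan. The Discussion argues that blinded reading makes a control group unnecessary. Blinding removes reader bias; it cannot separate ixekizumab from a co-treatment that changed.

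This is a matter for the protocol and not for the statistical analysis plan, because an analysis plan cannot restrict what patients are given.

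**Working it through.** **1. The rules side by side, for a patient who continues ixekizumab**

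| Co-treatment | Rule from month 4 to month 12 | Clear period before month-12 scan |
|---|---|---|
| Local glucocorticoid injection | allowed to month 11 | 1 month |
| csDMARD dose | none stated | none |
| NSAID dose | none stated | none |

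The csDMARD permission is worded as continuing existing treatment, but the exemption from the ban means that a new start is not excluded either. The open share of the primary interval is (12 - 4)/12 = 8/12. Clinic visits fall at months 4, 6 and 9.

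**2. The plan's own figures, for scale**

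Inputs from Sample size calculation: mean change 24.8, standard error 3.6 in 53 patients, 65 planned (at least 25 per diagnosis), 20% drop-out at month 12.

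- SD = 3.6 x sqrt(53) = 26.2, as stated.
- Paired t-test with noncentral t: 11 pairs give power 0.807 and 12 pairs give 0.847. The stated 12 pairs is reproduced to within one pair.
- Expected at month 12: 65 x 0.8 = 52 patients. SE = 26.2/sqrt(52) = 3.63, and the 95% half-width is 2.008 x 3.63 = 7.3.

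**3. Illustrative shift**

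The documents do not say how many patients would change dose or what a change does to the score. Assume a share q of 10-30% of all analysed patients and an effect d of 5-15 points per changed patient, all in the same direction. Shift = q x d:

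- 0.10 x 5 = 0.5 points (2% of 24.8)
- 0.20 x 10 = 2.0 points (8%)
- 0.30 x 15 = 4.5 points (18%, or 0.62 of the half-width)

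The sign may be either. A csDMARD or NSAID increase enlarges the fall; NSAID tapering may shrink it. Mixed directions partly cancel.

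**4. Does the test survive?**

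Take the largest shift off the expected fall: 24.8 - 4.5 = 20.3.

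- 52 patients: t = 20.3/3.63 = 5.6.
- A diagnosis group of 25 x 0.8 = 20: SE = 26.2/sqrt(20) = 5.86, t = 20.3/5.86 = 3.5, p = 0.003.

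**5. Which sensitivity rule?**

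One option is to give flagged patients the smaller of their month-4 and month-12 falls. With equal mean falls, SD 26.2 and correlation r, that value lies 26.2 x sqrt((1 - r)/pi) below the expected fall: 10.5 points at r = 0.5 and 4.7 at r = 0.9 (r assumed). With 10-30% flagged, the overall mean drops by 0.10 x 4.7 = 0.5 to 0.30 x 10.5 = 3.1 points even if background drugs do nothing. That is about as large as the shift it guards against. Using the month-4 change itself avoids this selection on the outcome.

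**The case against.** The strongest reply is that month 4 is the treat-to-target visit. Patients not in low disease activity change treatment and stay in the intention-to-treat analysis, so the month-12 result already reflects a treatment strategy. Fixing background doses would not turn it into a pure ixekizumab effect. That stands: switching is probably the larger attribution problem. It is a separate one, though, and resolving it would still leave the doses of continuing patients open.

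The continuing patients are also the least likely to need more treatment. They are in low disease activity at month 4, and Table 2 schedules no ASDAS, DAPSA, joint count or enthesitis assessment at months 6 or 9. Dose reduction is at least as plausible as escalation. This also stands and lowers the weight of the point. Likewise, 15 points for one dose change is about 60% of the whole expected fall (15/24.8), so the top of the illustrative range is generous.

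A reader might infer more than the documents support:

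- *That the primary test is unsafe.* Even the 4.5-point end is below the 7.3-point mean change that 52 patients need for significance, and the expected fall is far larger.
- *That doses will change, or that the effect is inflated.* The text permits changes; it does not plan them or give a direction.
- *That the per-protocol analysis cannot pick up dose changes.* The article does not define the per-protocol set, so this cannot be judged.
- *That doses go unrecorded.* The article says that "a summary of all measures to be collected is provided in Table 2", and that table has no row for concomitant doses. But it is a summary, and the case report form is not shown.

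**Conclusion.** The point holds as a modest one. The fixed-dose rule ends 8 months before the primary scan, in a single-arm study whose aim is to credit the change to ixekizumab. The same paragraph protects that scan from local injections but not from csDMARD or NSAID changes.

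The consequence is limited to how much of the month-12 fall is attributed to ixekizumab. It is probably small, its direction is unknown, and the documents do not allow it to be quantified. The range of 0.5 to 4.5 points rests wholly on the assumed shares and effects, and on the SD of 26.2 from the earlier golimumab study in axSpA. The conclusion that the tests stand rests on the same SD and on the expected fall of 24.8. This is a cheap improvement and not a flaw that undermines the trial.

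**What to change.** 1. In Study interventions, add: patients who continue ixekizumab after month 4 do not start a csDMARD or increase its dose until the month-12 procedures are done. Reductions for toxicity and treatment changes made under the month-4 decision rule are exempt.
2. In the same place, add: the NSAID dose is kept stable from month 11 until the month-12 procedures are done. This mirrors the injection rule.
3. Keep all scans in the intention-to-treat analysis. Add one sensitivity analysis that uses the month-4 change for patients who, after month 4, intensify background treatment or change treatment under the decision rule. It shows what had been reached under fixed doses; it does not estimate what continued ixekizumab alone would have given at month 12.
4. Show the planned month-4 change beside the primary result, as the estimate within the fixed-dose period.

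The cost is two sentences and one analysis on scans already planned, with no extra visit or scan. The downsides are a few more protocol deviations and a slight limit on co-treatment in patients already in low disease activity.
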